### Randomisation and allocation procedure

Cluster randomisation will be employed to ensure baseline comparability between the intervention and control groups for key characteristics, including age, weight, and known risk factors. The four selected farming communities will be stratified by geographic location (north and south of the district). Within each stratum, one community will be randomly allocated to the intervention group and one to the control group. Randomisation will be performed by an independent researcher using a computer-generated random number sequence. Allocation will be concealed from the field research team to reduce the risk of selection bias. Due to the nature of the intervention, blinding participants will not be feasible, as the differences between intervention and control conditions are easily observable. However, to minimise bias, the researcher responsible for delivering the intervention will be different from the researcher responsible for allocating clusters. Additionally, outcome data will be collected by individuals blinded to group assignment (44).

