## Research design and methods

### Study setting

The study will be conducted in the Ho West District of the Volta Region in Ghana. The Ho West district shares borders with the Republic of Togo, and its capital, Dzolo-Kpuita, is located 175 km northeast of Accra. The total population is 95,000 (20). Anaemia and undernutrition remain critical public health issues in this region. Recent national trends indicate that anaemia prevalence among children under 5 years, although decreasing, remains alarmingly high at 48.9% as of 2022, down from 76.1% in 2003 (21). In the Volta Region specifically, hospital-based data shows that over 55% of children under five are anaemic (22). Stunting, a marker of chronic undernutrition, also affects nearly one in five children under five in Ghana (23). In the Ho West district, 73.5% of the people work in agriculture in some capacity. Less than 1 % (0.06%) of households involved in agriculture are involved in fish farming, with the majority (95.2%) in crop farming (47). Farmers in this region cultivate a diverse range of fruits and vegetables, including bananas, pineapples, mangoes, pears, and oranges. These four farming communities, Abutia Kissiflui, Dededo, Amedzofe, and Kpedze, will be the focus of the study. The district’s busiest market, located in Abutia Kissiflui, generates up to 75% of the district’s tax revenue. Contributions from Dededo, Amedzofe, and Kpedze are 12.3, 8.7, and 4%, respectively. Kpedze has a population of 4,692 people, of which 12% are children under the age of five and 51% are women. There are 3,360 people living in Dededo, 16% of whom are children under five, and 53.3% of whom are women. A total of 1,561 people reside in Amedzofe, with 51.2% of them being women and children. With 1,667 residents, Abutia Kissiflui has a female population of 54% and a child population of 13.5% (20, 24). The district’s southernmost neighbourhoods, Kpedze and Amedzofe, were selected for the intervention group, while the northernmost neighbourhoods, Dededo and Abutia Kissiflui, were designated as the control group. Out of the 14 towns in the district, these towns were specifically chosen. To prevent contamination, the control and intervention groups were selected based on their proximity to one another and their geographic location. Also, data on nutritional treatments and services provided in each group will be recorded.

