### Sampling

A multistage sampling approach will be employed to select study participants. First, the Ho West District in the Volta Region of Ghana will be purposively selected due to its significance in fruit and vegetable production, retail activities, and rural household participation. Second, the district will be stratified geographically into northern and southern zones. From each zone, two communities (Amedzofe and Kpedze in the north; Abutia-Kissiflui and Dededo in the south) will be purposively selected based on agricultural diversity and accessibility.

From each of the four selected communities, farmers and traders will be randomly selected for the study. Systematic random sampling will be used to select households. A household list will be obtained with the assistance of community health volunteers or local authorities. Using a random start, every *nth* household will be selected. In each selected household, eligible participants, defined as women of reproductive age (with a child under five), will be invited to participate.

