### Intervention design and strategy

This study will implement a structured, community-based nutrition education and counselling program targeting women and children in the intervention communities of Kpedze and Amedzofe. In contrast, Abutia Kissiflui and Dededo will serve as control communities, with no intervention exposure. Such community-level strategies have been shown to improve food handling practices and reduce household-level losses in African settings (15). The aim is to enhance knowledge and practical skills on fruit and vegetable storage, reduce household-level post-harvest losses, and improve dietary practices.

The intervention will span a six-month period and will be coordinated by a trained dietitian, supported by three community health nurses. Educational meetings will occur monthly, and additional counselling will be provided through bi-weekly home visits and telephone interactions. Educational materials such as visual posters, handouts, and illustrative charts will be developed in local languages to ensure cultural relevance and ease of understanding. Group sessions will be interactive, allowing participants to ask questions and share experiences. Each session will last approximately 45 min and accommodate 5–10 women per group (Table 1).

**Table 1 tab1:** Lesson plan for nutrition education.

Month	Topic	Content	Rationale and literature support
Month 1	Importance of Fruits & Vegetables on Nutritional Status	Benefits, local examples, myths and facts	Dietary diversity and intake of micronutrient-rich foods like fruits and vegetables are critical for preventing undernutrition and anaemia in women and children (14). Awareness helps reshape food choices.
Month 2	Fruits and Vegetables Waste and Its Implications	Drivers, causes, prevention	Community-level losses reduce availability of key nutrients. Kitinoja and Kader (6) and Sheahan and Barrett (19) show that household knowledge on proper handling can reduce loss and improve food security.
Month 3–4	Fruit and Vegetable Preservation and Storage	Low-cost storage methods (e.g., clay pot coolers, FIFO), meal planning	Ambuko et al. (3) and Stathers and Mvumi (36) support the use of low-cost post-harvest technologies in rural African communities. FIFO principles help manage perishables better.

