### Statistical analysis

Statistical package for social sciences (SPSS) (IBM Corp. Released 2022. IBM SPSS Statistics for Windows, Version 30.0. Armonk, NY: IBM Corp) will be used for the data analysis. The Kolmogorov-Smirnov and Shapiro-Wilk tests will be used to assess the normality of the quantitative data. A *p*-value less than 0.05 indicates that the data is not normally distributed, and vice versa. The characteristics of the study participants will be analysed using descriptive statistics. A chi-square test will be done to assess the relationship between categorical variables. Fisher’s exact test will be employed to determine the significance level. Parametric tests will be used to analyse normally distributed data, and non-parametric tests will be used to analyse data that is not normally distributed. Parametric tests will be presented in terms of mean and standard deviation, and non-parametric tests will be presented in terms of median (maximum-minimum). A t-test will be conducted to compare the mean differences of the outcomes of interest within and between study groups at baseline and post-intervention. Regression analysis will be conducted to predict the drivers of fruit and vegetable loss, adjusting for age and gender. Partial correlation will be used to assess the strength of association among the variables. All *p*-values will be significant at *p* < 0.05.

The primary analysis will follow the intention-to-treat (ITT) principle, including all participants as initially allocated, regardless of their adherence to the intervention protocol. This approach ensures an unbiased estimate of the intervention effect. For secondary per-protocol analyses, only participants who fully adhered to the intervention will be considered. To address missing data, particularly in outcome measures such as dietary assessments and anthropometry, multiple imputation methods will be employed under the assumption that data are missing at random. Sensitivity analyses will be conducted to assess the robustness of results. This strategy helps maintain the validity and reliability of findings despite potential data gaps.

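### With two communities per arm, randomisation cannot ensure baseline comparability, and the planned comparison of arms is a t-test that names no covariates

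*Protocol article*

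**What the plan says.** Under Randomisation and allocation procedure, the protocol article states that "Cluster randomisation will be employed to ensure baseline comparability between the intervention and control groups for key characteristics", with age, weight and known risk factors given as examples. The four communities are stratified into a northern and a southern zone, and "Within each stratum, one community will be randomly allocated to the intervention group and one to the control group". The Sampling section gives the zones as "Amedzofe and Kpedze in the north; Abutia-Kissiflui and Dededo in the south".

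Study setting describes the communities' economic weight. The district's busiest market is "located in Abutia Kissiflui, generates up to 75% of the" district's tax revenue. For the other three, "Contributions from Dededo, Amedzofe, and Kpedze are 12.3, 8.7, and 4%, respectively". Study setting and Intervention design and strategy both name the arms. In the latter, Kpedze and Amedzofe receive the programme, while "Abutia Kissiflui and Dededo will serve as control communities, with no intervention exposure".

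For the analysis, Statistical analysis says: "A t-test will be conducted to compare the mean differences of the outcomes of interest within and between study groups at baseline and post-intervention". The only covariates named there, age and gender, belong to the regression on drivers of loss. The same section lists descriptive statistics and chi-square or Fisher tests. It also offers repeated-measures analysis or a Bonferroni correction for outcomes measured at more than one time, and says that it covers methods for baseline comparability. Under Sociodemographic characteristics, age, education, occupation and income are among the items collected.

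**The concern.** Randomisation balances covariates in expectation. How close one realised allocation comes to balance depends on how many units are randomised, and here there are four. A claim that comparability is ensured tells the analyst and the reader that a difference between arms after the intervention needs no further defence. The choice of a t-test without covariates fits that belief.

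What is at stake is attribution. Dietary diversity, fruit and vegetable intake and household waste could all plausibly depend on the kind of community a household lives in. If the arms differ in this respect, some of the difference between them may belong to the communities and not to the education. The section on concomitant care nevertheless says that restricting outside programmes lets the measured effects be credited to the intervention alone, and the limitations section does not mention differences between arms.

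**Working it through.** The plan states no balance figure to reproduce, so the check has three parts.

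**1. Possible splits of the revenue shares.** Inputs from Study setting: Abutia Kissiflui 75 (a ceiling), Dededo 12.3, Amedzofe 8.7, Kpedze 4. The sum is 75 + 12.3 + 8.7 + 4 = 100. There are three distinct two-against-two splits:

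- Abutia Kissiflui + Kpedze against Dededo + Amedzofe: 75 + 4 = 79.0 against 12.3 + 8.7 = 21.0
- Abutia Kissiflui + Amedzofe against Dededo + Kpedze: 75 + 8.7 = 83.7 against 12.3 + 4 = 16.3
- Abutia Kissiflui + Dededo against Amedzofe + Kpedze: 75 + 12.3 = 87.3 against 8.7 + 4 = 12.7

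The zones pair Amedzofe with Kpedze, and Abutia Kissiflui with Dededo. The stated rule takes one community per zone into each arm, so only the first two splits can arise from it. The third is the allocation named in the article. It puts each zone wholly in one arm, which the rule cannot do.

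**2. Sensitivity to the ceiling.** Lower the 75, hold the other three (sum 25) and rescale. The best split is (x + 4)/(x + 25) and the named split is (x + 12.3)/(x + 25).

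- x = 50: best 54/75 = 72:28; named 62.3/75 = 83:17
- x = 40: best 44/65 = 68:32; named 52.3/65 = 80:20
- x = 30: best 34/55 = 62:38; named 42.3/55 = 77:23

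Near balance (51:49) appears only when x falls to about 16.

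**3. Covariates in general.** The documents give no intracluster correlation (ICC), so I assume 0.05 and 0.10. I also assume 35 households per community (70 per group over two communities). Treating communities as independent draws, the difference between arms in a standardised covariate has

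SD = sqrt(2 × (ICC/2 + (1 − ICC)/70)).

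- ICC 0.05: sqrt(2 × (0.0250 + 0.0136)) = 0.28. Chance of an imbalance beyond 0.25 SD in either direction: 37%
- ICC 0.10: sqrt(2 × (0.0500 + 0.0129)) = 0.35. Chance: 48%
- 140 households randomised individually (ICC 0): sqrt(2/70) = 0.17. Chance: 14%

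Stratification would lower the first two figures if communities within a zone resemble each other.

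Testing at baseline would not settle the matter. A two-sample t-test with 70 per group, ignoring clustering, detects a true imbalance of 0.3 SD with power of about 0.42.

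**The case against.** The strongest reply has four parts.

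First, the claim concerns age, weight and risk factors, whereas the illustration uses tax revenue. The article gives no measure of household market access such as distance, price or availability. The four shares also sum to 100% although the district has 14 towns, so their exact meaning is unclear. This stands. The shares are a proxy for market size and serve only as an illustration. The claim fails because of the number of communities, whatever the shares mean.

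Second, a reader might infer that one arm must hold at least 79% of the revenue, or that 87:13 is what the randomisation yields. Neither is supported. The 75% is a ceiling, so it cannot give a minimum, and 87:13 comes only from the named allocation.

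Third, a reader might infer that the trial will mistake any gap between market-town and other households for an effect of the education. That goes too far. The repeated-measures option, or a t-test on change, would remove stable differences in outcome level. What remains exposed is change over time that differs by community. Nor does the article say that a non-significant baseline test would be taken as proof of balance, and t-tests are not its only descriptive tool.

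Fourth, a covariate list is often left to a statistical analysis plan, which is not shown here. That is fair for the detail. But the article itself names the method for comparing arms and itself asserts comparability, so the point concerns what it states.

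**Conclusion.** The statement that cluster randomisation ensures baseline comparability is wrong for a design with two communities per arm, and the stated comparison of arms makes no allowance for imbalance in household covariates. This does not depend on how the conflict over the allocation is resolved: the two splits that the rule permits are also unequal, at 79:21 and about 84:16 with 75% at face value, and 62:38 at best with 30.

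The chances of 37% and 48% for a covariate imbalance above 0.25 SD, against 14% under individual randomisation, rest on assumed ICCs and show the order of magnitude only. The documents do not show that the arms differ in market access, or that the result will be biased in a particular direction. They show that comparability is claimed where the design cannot deliver it, and that attribution to the intervention alone is not secured. This should be corrected, and it can be done before any results are seen, since the article reports that nothing has yet been analysed.

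**What to change.** 1. Randomisation and allocation procedure: replace the claim of ensured comparability with a statement that four communities cannot be expected to balance. Reconcile the one-per-zone rule with the allocation named in Study setting and in Intervention design and strategy.
2. Statistical analysis: make the arm comparison a model adjusted for the baseline value of the outcome and a short set of household covariates already collected (woman's age, education, income, occupation, child's age). Fix the set now and use it whatever the baseline tests show. If an unseen analysis plan already does this, bring the article into line with it.
3. Limitations, and the statement on attribution under concomitant care: say that community-level differences such as market size remain unadjusted, so effects cannot be credited to the intervention alone. Household covariates cannot remove a difference between communities when there are only two per arm.

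The cost is a few degrees of freedom and a less favourable account of the design. No new data are needed. The change deals with household-level imbalance only and does not make up for having four clusters.

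### The arms named in the protocol cannot result from its stated stratified randomisation, so the trial's randomised status is not established

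*Protocol article*

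**What the plan says.** Four sections of the protocol article bear on allocation.

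- **Randomisation and allocation procedure** gives the rule. The four communities are stratified by location, north and south, and "Within each stratum, one community will be randomly allocated to the intervention group and one to the control group". An independent researcher is to do this with a computer-generated sequence, concealed from the field team. The stated purpose is comparability: "Cluster randomisation will be employed to ensure baseline comparability between the intervention and control groups".
- **Study setting** gives the result and a reason. The "southernmost neighbourhoods, Kpedze and Amedzofe, were selected for the intervention group", and the "northernmost neighbourhoods, Dededo and Abutia Kissiflui, were designated as the control group". To limit contamination, "the control and intervention groups were selected based on their proximity to one another and their geographic location".
- **Sampling** assigns communities to zones: "Amedzofe and Kpedze in the north; Abutia-Kissiflui and Dededo in the south".
- **Intervention design and strategy** repeats the arms. The programme targets "women and children in the intervention communities of Kpedze and Amedzofe", with Abutia Kissiflui and Dededo as controls.

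The Abstract and Study status and timeline call the study randomised. Statistical analysis says that the intention-to-treat analysis gives an unbiased estimate of effect.

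**The concern.** The article states an allocation rule and an allocation result that exclude each other. Stratifying by zone is meant to give each arm one community from each zone. The named arms do the reverse, with one whole zone in each arm.

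The label randomised, the expected baseline comparability and the claim of unbiasedness all depend on the stated mechanism. If arms follow zones, every difference between arms is also a difference between zones, and anything that differs between the zones could produce it. A reader of the results would take a comparison of two areas as randomised evidence.

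**Working it through.** The plan gives no figure to reproduce here. The check is whether the stated rule can yield the stated arms.

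**Inputs**
- Communities: Amedzofe, Kpedze, Abutia Kissiflui, Dededo.
- Rule (Randomisation and allocation procedure): two strata, with one intervention and one control community in each.
- Zones according to Sampling: north = {Amedzofe, Kpedze}; south = {Abutia Kissiflui, Dededo}.
- Zones according to Study setting: south = {Amedzofe, Kpedze}; north = {Abutia Kissiflui, Dededo}.
- Named intervention pair (Study setting; Intervention design and strategy): Kpedze and Amedzofe.

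**Step 1: possible splits.** Choosing 2 of 4 communities for intervention gives 4!/(2! × 2!) = 6 splits.

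**Step 2: splits that the rule allows.** One intervention community from each zone gives 2 × 2 = 4:
1. Amedzofe and Abutia Kissiflui
2. Amedzofe and Dededo
3. Kpedze and Abutia Kissiflui
4. Kpedze and Dededo

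The list is the same under both sets of labels, because swapping north and south leaves the pairs unchanged.

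**Step 3: is the named pair allowed?** Kpedze with Amedzofe is 0 of the 4, so its probability under the stated rule is zero.

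**Step 4: consequence for estimation.** Code arm as 1 for intervention, and zone as 1 for the zone that contains Amedzofe and Kpedze.
- Named allocation, in the order Amedzofe, Kpedze, Abutia Kissiflui, Dededo: arm = (1, 1, 0, 0) and zone = (1, 1, 0, 0). Their correlation is 1.0, and the matrix [intercept, arm, zone] has rank 2 of 3. Arm and zone effects cannot be estimated separately.
- An allowed allocation, for example Amedzofe and Abutia Kissiflui: arm = (1, 0, 1, 0) and zone = (1, 1, 0, 0). The rank is 3, so the two are separable.

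**The case against.** **A reader might infer that the trial was not randomised.** The article does not show that. It gives two accounts, a computer-generated draw and a selection by geography, and does not say which took place. Naming the arms is no evidence of deliberate choice: Version 1.0 is dated June 9, 2025, after recruitment was complete, so the arms would be known by then. The sentence giving the geographic reason follows one about choosing these towns out of 14, and may partly concern site selection. This objection stands, and it limits the conclusion to randomised status not being established.

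**A draw of another kind could have produced these arms.** One draw between whole zones would give exactly two areas, one per arm, and could yield the named allocation. That would be randomised, but it is not the stated rule. It would leave one randomised unit per arm, with zone still aliased with arm.

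**The north/south labels may simply be a slip.** They probably are a slip in one of the two sections, but correcting it does not help. Both sections keep the same pairs together.

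**A reader might take the tax-revenue shares in Study setting as the size of the harm.** The control communities account for up to 75 + 12.3 = 87.3%. But Abutia Kissiflui alone supplies up to 75%, so the arm that holds it dominates under any allocation. Under the allowed splits that arm would hold up to 75 + 8.7 = 83.7% or 75 + 4 = 79%. Most of the contrast would therefore remain under correct stratified randomisation. Tax revenue is also neither an outcome nor a measure of household access to produce.

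**Conclusion.** The contradiction is certain on the text. The stated rule allows 4 allocations, and the named one is none of them under either set of zone labels. No other section reconciles this. It is also not a detail that an article could leave to a fuller document, because the mechanism and the result are both stated and conflict.

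It follows that randomised status is not established. Conditional on the named arms being those in use, arm and zone are completely aliased, and the claims of comparability and unbiasedness lack support. The aliasing needs only that the pairing of communities into zones is correct, on which both sections agree. The direction and size of any resulting bias cannot be derived from the document.

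**What to change.** Establish and report the mechanism actually used. Then make Study setting, Sampling, Randomisation and allocation procedure, and Intervention design and strategy agree, including on which zone is north. What follows depends on the answer:

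- **(a) Communities were assigned by location.** Remove the text on stratified randomisation and concealment. Describe the study in the Abstract and in Study status and timeline as a non-randomised controlled before-and-after study. Bring the registry record into line if it says otherwise; its content was not available here. Base inference on baseline-adjusted differences, and state that zone and arm cannot be separated.
- **(b) Whole zones were drawn.** Say so, and state that there is one randomised unit per arm and that zone remains aliased with arm.
- **(c) A draw within strata took place.** Document it, and correct whichever of the arm names or zone memberships is factually wrong. Zones must not be redefined to fit the arms.

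The cost is protocol wording and, under (a) or (b), a weaker causal claim. No new data are needed.

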### Recruitment of participants

The objective of the study will be explained to farmers, traders, and women within various households in the communities. Those who give their consent will qualify to participate in the study. The recruitment of participants will last for 1 month. To ensure adequate enrolment, the study will use community engagement through local leaders and health workers, public sensitisation via meetings and local radio, and clear communication in local languages. A multistage sampling method will ensure fair representation, while flexible scheduling and follow-up reminders will help reduce non-response and support retention.

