### Procedure for nutrition counselling session

Counselling sessions will be conducted privately, either in community meeting spaces or during home visits. Each session, lasting up to 30 min, will be delivered in a participant’s preferred language to ensure comprehension.

The key steps will include:

Obtaining written or thumbprint consent from participants.Conducting a brief dietary assessment.Providing tailored guidance on post-harvest handling, appropriate storage methods, and reducing waste.Distributing a simple dietary guide/manual developed for the study.Following up with progress reviews every two to three weeks via calls and home visits.

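### Allocation is said to be concealed from the field team, but the documented account of how the villages got their arms does not support that safeguard at household consent

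*Protocol article*

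**What the plan says.** All references are to the protocol article.

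- **Randomisation and allocation procedure.** The four communities are the units of allocation. They are stratified north and south, and within each stratum one goes to each arm by an independent researcher's computer-generated draw. The section adds: "Allocation will be concealed from the field research team to reduce the risk of selection bias". It also accepts that participants cannot be blinded.
- **Study setting.** The arms are reported in the past tense and by name: "Kpedze and Amedzofe, were selected for the intervention group, while the northernmost neighbourhoods, Dededo and Abutia Kissiflui, were designated as the control group". The stated basis is that "the control and intervention groups were selected based on their proximity to one another and their geographic location".
- **Intervention design and strategy.** The same arms are repeated. The programme is described as "targeting women and children in the intervention communities of Kpedze and Amedzofe", while "Abutia Kissiflui and Dededo will serve as control communities, with no intervention exposure".
- **Sampling.** Amedzofe and Kpedze lie in one zone, Abutia-Kissiflui and Dededo in the other. Households are taken from a list at a fixed interval after a random start.
- **Recruitment of participants.** "Those who give their consent will qualify to participate in the study", and to reach the target "the study will use community engagement through local leaders and health workers".
- **Statistical analysis.** The primary analysis is by intention to treat, which is said to ensure an unbiased estimate of the effect.

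**The concern.** In a cluster trial, concealment protects entry only if households are identified and consented before anyone involved knows the village's arm. Once a village's arm is known, so is the arm of every household in it. The article claims this protection, yet its own account of the arms points to assignment by geography, which could have been known before any household was approached.

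What is at stake is who enters each arm. A woman in an intervention village may agree because she wants the education. A woman in a control village is asked for interviews and finger-prick blood samples and is offered no programme. If agreement differs by arm for such reasons, the groups differ in motivation, diet or health before any session is held. An intention-to-treat analysis keeps everyone enrolled in their arm, but it cannot recover those who never enrolled.

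**Working it through.** There is no stated figure to reproduce. The check compares the sections and counts the allocations that the rule allows.

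**1. Allocations allowed by the stated rule.** Inputs: two strata of two villages (Sampling), one village to intervention in each (Randomisation and allocation procedure). Number allowed: 2 × 2 = 4. The possible intervention pairs are:
- Amedzofe + Abutia-Kissiflui
- Amedzofe + Dededo
- Kpedze + Abutia-Kissiflui
- Kpedze + Dededo

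**2. The allocation that is named.** Study setting and Intervention design and strategy both give Kpedze + Amedzofe. Without strata, two villages can be chosen from four in 6 ways. The rule excludes the two that take a whole zone, and the named pair is one of those. Its probability under the stated rule is 0. Study setting and Sampling use opposite compass labels for the two pairs, but the pairs are the same, so the labels do not affect this result.

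**3. What could be known at consent.**
- *Arms set by location (Study setting).* Arm and zone coincide, so a household's village gives its arm with certainty. There is no draw to conceal.
- *Arms drawn within strata (Randomisation and allocation procedure).* Before disclosure, each village has probability 1/2 of intervention. After disclosure, every household's arm is certain, and one village's arm reveals that of its stratum partner. Concealment works here only if consent came before disclosure.

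The text does not say which came first.

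**4. Illustrative size, on assumed consent rates.** Take the article's national figure of 48.9% anaemia in children under five. Assume 90% consent everywhere except in control households with an anaemic child, where it is c. Anaemia among enrolled controls is 0.489c / (0.489c + 0.511 × 0.9).

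| c | Enrolled control anaemia | Baseline gap |
|---|---|---|
| 0.90 | 48.9% | 0 points |
| 0.70 | 0.3423 / 0.8022 = 42.7% | 6.2 points |
| 0.50 | 0.2445 / 0.7044 = 34.7% | 14.2 points |

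For a continuous outcome, suppose 10% of one arm is lost selectively. If those lost average 1 SD below those who stay, the arm mean shifts by 0.10 × 1 = 0.10 SD. If exactly the lowest tenth is lost, it shifts by φ(1.2816)/0.9 = 0.195 SD. In a two-sided 5% t-test with 70 per arm and no true effect, the noncentrality is d × √(70/2), which is 0.59 and 1.15. The rejection rates are 9.0% and 20.9%. This ignores clustering and uses post-intervention values alone, so these are not this trial's error rates. The 10% is the sample-size section's non-response allowance, not an observed refusal rate.

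**The case against.** The strongest reply is that the order of events may be sound and simply not visible here. This is a condensed article. Its schedule (Figure 1) and flow chart (Figure 2) are not shown and could place enrolment before allocation. The version is dated June 9, 2025, and recruitment was already complete at submission. Arms named in a document of that date do not show what recruiters or women knew at enrolment. This stands. A reader might infer that every household's arm was in fact predictable at recruitment, and the documents do not establish that. What they do contain is a positive claim of concealment beside an account of arm-setting that contradicts the draw it would protect.

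Systematic sampling is also a real safeguard. It limits whom the field team can approach, although it does not govern who agrees.

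Two further inferences are tempting and not supported:

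- *The counselling consent filters one arm.* Procedure for nutrition counselling session lists "Obtaining written or thumbprint consent from participants", and only the intervention arm is counselled. But Ethics and dissemination requires consent from all participants before enrolment, so this step comes after entry. The intention-to-treat rule already keeps women who decline counselling.
- *The claim of an unbiased estimate is derived from concealment.* Statistical analysis attributes it to intention to treat. The narrower point is that intention to treat cannot deliver it if enrolment differed by arm.

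Finally, the main nutritional outcomes are measured at baseline and after the intervention. A stable entry difference would be visible at baseline and would largely cancel in a comparison of change. That reduces the harm. It does not remove differences in motivation that affect how women respond over six months.

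**Conclusion.** The concern holds in conditional form. The concealment sentence is not supported by the design as documented: villages are the unit, location is given as the basis for the arms, and the named arms cannot come from the stated draw. If the arms were set by location before household recruitment, concealment offered no protection against differential consent, and intention to treat does not repair it.

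This rests on the text alone and would change if the sponsor can show that households were consented before the arms were known. Differential consent is a risk that nothing in the article shows to have happened. Its size cannot be derived from the documents, and the figures above only show that moderate selectivity could matter. The point concerns entry to the trial, not blinding of outcome collection. It should be corrected because the change is cheap and affects what the trial can claim.

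**What to change.** 1. Reconcile Study setting, Sampling, and Randomisation and allocation procedure on how the arms were set, and state when they became known relative to household consent.
2. Unless households were consented before the arms were known, withdraw the concealment sentence or, if a draw of villages took place, limit it to the allocator's draw. Also remove the word unbiased from Statistical analysis.
3. Report households drawn, reached, ineligible and refused by village, as far as records allow. The article does not say that refusals were logged, so gaps should be stated.
4. Compare post-intervention outcomes with adjustment for the baseline value already collected. Entry differences then become visible and are partly corrected. A refusal rate alone implies no size of bias, so it cannot by itself set a sensitivity shift.

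The cost is protocol wording, a tally from whatever recruitment records exist, and slightly more analysis. No new participants or measurements are needed. The downside is a less favourable description of the design.
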